## 2. PROJECT SUMMARY

COVID - 19 is a new type of viral pneumonia described in December 2019 in Wuhan - China; it represents a major public health problem due to its rapid spread and the ability to generate severe pneumonia in susceptible patients; at the moment, no specific treatment for the virus has been described, its management being mainly a supportive one. Our objective is to estimate whether treatment with hydroxychloroquine 400 mg / day for 10 days compared to placebo reduces in-hospital mortality in subjects with severe respiratory disease due to COVID-19. Secondary outcomes will be days of mechanical ventilation, requirement of mechanical ventilatory support, days of hospitalization and the cumulative incidence of serious adverse events.

**Design:** Double-blind randomized controlled trial to evaluate the safety and efficacy of hydroxychloroquine for the treatment of severe disease by COVID-19.

**Subjects eligible** Adults older than 18 years with a diagnosis of severe disease (requiring hospitalization or intensive care) of COVID-19 (confirmed by RT-PCR). Subjects will be stratified into two groups (subjects not requiring or requiring ventilatory support at the time of randomization). The analysis will be carried out in R-Rstudio statistical software, considering an interim analysis when half of the sample size is recruited (150 per group).

### **3. DESCRIPTION OF THE PROJECT**

#### **3.1 INTRODUCTION AND BACKGROUND**

The outbreak of respiratory infection by the coronavirus 2019 (SARSCOV-2) started in December 2019, in Wuhan City, Hubei Province (China) [1-5]. From this city, the outbreak has been spreading to various provinces of China and other countries [6]. As of February 16, 2020, 28 countries had been recognized with confirmed cases, with 70,548 infections and 1,770 deaths in China, and 413 infections in Japan. [6]. By March 24, > 190 Countries have been affected.

As in other coronaviruses, SARS and MERS, the original human infection was probably obtained from contact with animals, but effective human-to-human transmission has been demonstrated, with a growth rate greater than 1, estimated in 2.6[7], and a rapid duplication of cases that ensure not only the maintenance of the epidemic but also its expansion.

Until now, there is no effective treatment available for COVID-19, however the in-vitro effectiveness of Remdesivir and chloroquine was recently reported, the latter in concentrations capable of being obtained in in-vivo patients who use it [8]. Chloroquine and hydroxychloroquine are originally antimalarial drugs. They have had regular use for decades with a well documented benefit/risk profile, at a very low cost, and if they are proven effective in vivo, they could be very useful drugs. The broad antiviral effect has been attributed to increased pH of endosomes, which are required for virus-cell fusion and also by interference with glycosylation of SARS-VOC cell receptors.[9-11] In addition to the antiviral effect, immunomodulatory effects have been found that could enhance the antiviral effect and the systemic impact of serious infections.

The range of 2019-CoV clinical presentations is wide, from asymptomatic infections to fatal infections, with severe lung damage, respiratory failure, and multi-organ failure. As in severe influenza, severe damage has been associated with a systemic inflammatory reaction or cytokine storm, which could be attenuated by the immunomodulatory and anti-inflammatory effect of chloroquine or hydroxychloroquine.

The overall fatality rate of COVID-19 disease has been estimated at around 2.3%, but in severe cases of respiratory failure, requiring hospitalization or critical care, it is considerably higher, between 10-15%, but could easily increase to 20-30% in those requiring intensive care and mechanical ventilation.

A letter was recently published [12] Describing that on February 17, the Chinese State Council issued a press release stating that Chloroquine had demonstrated marked efficacy and acceptable safety for the treatment of COVID-19 pneumonia in multicentre trials in China with more than 100 patients out of 10 hospitals, but no report in a peer reviewed journal has appeared.

#### **3.2 JUSTIFICATION**

There is no approved pharmacological treatment for COVID-19, and based on the in-vitro effectiveness of chloroquine, its proven safety for decades, its low cost, a double-blind RCT is proposed to evaluate the efficacy and safety of Hydroxychloroquine derived

compound, generally with better tolerance and safety, in hospitalized patients with severe respiratory disease due to COVID - 19.

### 3.3 GENERAL OBJECTIVE

Estimate whether 10-day treatment with 400 mg / day of hydroxychloroquine (HCQ), 200 mg BID, reduces the 30 day mortality in hospitalized patients with severe COVID-19 disease.

#### 3.3.1 SPECIFIC OBJECTIVES

- A) Assess whether days of hospitalization are decreased with HCQ compared to placebo.
- B) Assess whether days of supplemental oxygen therapy are decreased with HCQ compared with placebo.
- C) Assess whether the days for viral test negative (one per week) decrease with HCQ compared with placebo
- D) Assess if the need of ventilatory support with HCQ is decreased compared with placebo.
- E) Assess if the days of mechanical ventilation in patients treated with HCQ decrease compared with placebo.
- D) Evaluate the safety of HCQ.

### 3.4 THEORETICAL AND CONCEPTUAL APPROACH

Phase III, multicenter, randomized, double-blind, controlled clinical trial; The coordinating center will be INER and it is expected to recruit other hospital centers in Mexico City and in other states. Planned to be carried out in critical areas (Emergencies, intensive care, postoperative recovery) and in Hospitalization services of the National Institute of Respiratory Diseases Ismael Cosío Villegas and participating hospitals.

Subjects eligible will be adults over 18 years of age with a confirmed diagnosis of COVID-19 by RT-PCR (in a pharyngeal, nasopharyngeal sample or in a tracheal aspirate / bronchial lavage) that requires hospitalization for severe or critical COVID-19.

1. **Blinding:** Patients who agree to participate, who are hospitalized at INER or collaborating centers, with a diagnosis of severe disease due to COVID-19 will be randomized. The randomization will be centralized, carried out by a dedicated software, and randomization will be utilized to label the experimental drug and the placebo. The treating doctors, the nursing staff and the rest of the treating team and the evaluators of the outcomes will be blinded to the group corresponding to each one of the subjects.

**2. Risk stratification** Subjects included in two groups will be stratified for randomization:

- a. Stratum A: Subjects diagnosed with severe disease by COVID-19 requiring hospitalization that do not require invasive ventilatory management.
- b. Stratum B: Subjects diagnosed with severe disease by COVID-19 requiring invasive ventilatory management and / or management in the intensive care respiratory unit at the time of randomization.

**3. Main outcome:**

- a. Mortality rate at 30 days after randomization.

**4. Secondary outcomes:**

- a. Proportion of patients needing invasive ventilatory support (stratum A only)
- b. Duration in days of invasive mechanical ventilation for patients requiring such procedure
- c. Time in days from randomization to hospital discharge.
- d. Time in days from randomization to end of oxygen therapy
- e. Time in days to negative viral test using weekly RT-PCR testing
- f. Incidence of AEs and AEs leading to treatment discontinuation
- g. • Incidence of serious adverse events

**5. Tests carried out:**

- a. Panel of 10 respiratory viruses and 2019-nCoV
- b. Every week: RT-PCR viral test in pharyngeal, nasopharyngeal aspirate, and in bronchial sample or bronchial lavage or tracheal aspirate in intubated.
- c. Routine tests (Blood cell count, blood chemistry and liver function tests and ECG or cardiac monitoring)

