**6. Specific protocol interventions:**

- a. Subjects entering the experimental group will receive hydroxychloroquine orally or by nasogastric tube (refer to the protocol procedures manual for the method of crushing tablets and administration via nasogastric tube), 200 mg every 12 hours, for 10 days. The placebo group will receive an identical placebo for 10 days. 10 days are tentatively proposed although the working groups suggest a use between 5 to 14 days; the box of hydroxychloroquine contains 20 tablets of 200mg; We justify the 10-day period because it is somewhere in between the various recommendations and because it is more practical to use one box per subject
- b. Patients in both strata will be treated according to protocols of participating institution under the responsibility of the physician in charge: all interventions, medications for all purposes, or non-drug interventions will be registered.
- c. Patients will be followed up to 30 days after randomization by telephone if discharge occur earlier than Day 30
- d. The Investigator is responsible for detecting, documenting, and recording events that meet the definition of an AE or SAE and remain responsible for following up AEs that are serious, considered related to the study

intervention or study procedures, or that caused the participant to discontinue the study

- e. Adverse events will be reported to CE and to manufacturer of the drug (Sanofi México, S.A. de C.V.)

**Statistical analysis:** The analysis will be carried out in R-Rstudio statistical software. Descriptive statistics will be used according to the type of variable and distribution.

The main outcomes will be compared using parametric and non-parametric tests according to the type of variable and distribution.

Death rate (at 30 days), the primary outcome, will be compared between treatment groups using a logistic regression model, adjusting for age, time from onset of symptoms to randomization, comorbidities (diabetes, hypertension, obesity, tobacco smoking) taking into account the randomization strata.

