## **2. Entry criteria**

- a. At least 18 years old
- b. Signed informed consent.
- c. Confirmed infection of COVID-19 by RT-PCR and pharyngeal and nasopharyngeal specimen, or in bronchoalveolar lavage or tracheal aspirate.
- d. Documented lung infection due to opacities in the chest plate or in a chest computed tomography without contrast medium
- e. Hypoxemic type respiratory failure, documented by a SaO2 <90% in ambient air, or a PaO2 / FIO2 <250, at an altitude of 2240 m, in the Valley of Mexico or Puebla, or values equivalent to other altitudes above the sea level
- f. <14 days from onset of symptoms

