## **3. Exclusion criteria:**

- a. Positive pregnancy test.
- b. Contraindication to start or continue hydroxychloroquine (including but not limited to history of pre-existing maculopathy, history of prolonged QTc syndrome or other cardiac condition that, by the judgement of the Investigator, would put the patient at higher risk for QTc prolongation or sudden cardiac death, severe skin reactions, patient with uncorrected hypokalemia or hypomagnesemia, a contraindicated drug interaction according to local drug labelling, , known hypersensitivity to hydroxychloroquine or chloroquine, severe hepato-cellular disorder, severe renal insufficiency
- c. Previous COVID-19 infection
- d. Decision of the responsible doctor not to participate.
- e. Transfer of the patient to another hospital unit
- f. Current or last month treatment with hydroxychloroquine.

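### Item 5c accepts cardiac monitoring in place of an ECG and asks for no QTc before the first dose, so exclusion b may have no reading to act on

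*Protocol*

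**What the plan says.** The cardiac test is set in section 3.4 of the protocol, under Tests carried out, item 5c: "Routine tests (Blood cell count, blood chemistry and liver function tests and ECG or cardiac monitoring". The item names no QTc, no frequency and no time relative to randomization or first dose. The line above it, 5b, does give a frequency for the viral test (weekly).

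QTc appears in one other place in the text available, exclusion b. That criterion opens "Contraindication to start or continue hydroxychloroquine (including but not limited to history of pre-existing maculopathy" and goes on to "history of prolonged QTc syndrome or other cardiac condition that, by the judgement of the Investigator"; such a condition counts if it is thought to make a long QTc or sudden cardiac death more likely. It also lists uncorrected low potassium or magnesium and drug interactions that the local label rules out.

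Treatment is 200 mg every 12 hours for 10 days (item 6a). The settings are given in section 3.4: "Planned to be carried out in critical areas (Emergencies, intensive care, postoperative recovery) and in Hospitalization services", at the coordinating center and at other hospitals. Care other than the study drug follows each institution's own protocols (item 6b).

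**The concern.** Exclusion b shows that the authors regard QTc prolongation and sudden cardiac death as hazards of this drug in these patients. A criterion of that kind can act only on what is known about the patient. Where the long QTc has never been recorded, there is no history to find, and judgement cannot weigh a value that nobody has read.

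Item 5c is where the protocol could supply the reading. Instead it lets each site choose between an ECG and monitoring, and asks for a recorded QTc from neither. Recruitment covers ordinary wards as well as critical areas, at several hospitals, so practice may differ between sites. What is at stake is the safety of individual patients, not the inference of the trial.

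**Working it through.** The protocol gives no figure on this point to reproduce. The check is a reading of the text, with two simple counts.

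1. **What 5c requires.** The two cardiac options are joined by *or*, so either one satisfies the item. A QTc is not asked for under either. No test in 5c has a stated time, so even a site that chooses the ECG could take it after the first dose. The gap thus has three parts: the alternative, the missing reading and the missing timing. Deleting the alternative alone would not close it.

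2. **What the criteria require.** Entry items a to f and exclusion items a to f make 6 + 6 = 12. At least five rest on a test or its result:
   - entry c: RT-PCR;
   - entry d: imaging ("Documented lung infection due to opacities in the chest plate or in a chest computed tomography without contrast medium");
   - entry e: oxygen saturation or the PaO2/FIO2 ratio;
   - exclusion a: "Positive pregnancy test";
   - exclusion b: potassium and magnesium.

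   Items asking for an ECG or a measured QTc: 0 of 12.

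3. **What exclusion b can catch.** It covers a known QTc history, a cardiac condition that the investigator judges risky, an uncorrected electrolyte disorder and a contraindicated co-medication. Its list is open and applies both to starting and to continuing the drug, so a long QTc that someone has recognised can already exclude the patient or stop treatment. What remains is a long QTc from another cause that has not been recognised. The gap is one of detection, not of authority to act.

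4. **Whether later provisions fill it.** Item 6d on adverse events acts after an event. The independent committee looks at the data at mid-trial. Neither screens a patient before dose 1.

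5. **Exposure.** 2 doses per day × 10 days = 20 doses, in a planned 300 patients on hydroxychloroquine. The number starting without a QTc read lies anywhere from 0 (every site takes and reads an ECG first) to 300 (none does). That range carries no information, and the documents give no prevalence of long QTc, so no estimate of patients affected is offered.

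**The case against.** The case on the other side has real force.

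- **Exclusion b already guards against QTc risk in several ways.** This stands. A reader might infer that for QTc the protocol relies on history and judgement alone. It does not: the electrolyte and drug-interaction items bear on the same risk. They reduce it but do not reveal a long QTc of other origin.
- **Item 5c is a summary list.** Blood chemistry there does not name potassium or magnesium either, although exclusion b depends on both. That is a fair reply to a complaint about missing detail. It does not answer the alternative itself: the laboratory tests in 5c have no substitute, and the cardiac test does.
- **Monitoring may display a QTc, and sites may take an ECG anyway.** Nothing in the documents says otherwise. A reader might infer that sites will omit the ECG; the text does not support that. It permits the omission without showing that it happens.
- **Not all of the text was available.** The part of the protocol between the exclusion criteria and section 5, and the procedures manual, were not at hand, and either may require an ECG. The manual is cited in the text available only for one purpose: "refer to the protocol procedures manual for the method of crushing tablets and administration via nasogastric tube". This limits how firmly absence can be claimed, but it does not change the wording of 5c. If another part requires an ECG, 5c should be brought into line with it.

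The point cannot be left to a statistical analysis plan, since screening tests are protocol procedures.

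**Conclusion.** The point holds in a limited form. Under the text available, cardiac monitoring may stand in for an ECG, no QTc need be read, and nothing places the test before the first dose. A patient with an unrecognised long QTc could therefore start hydroxychloroquine, against the aim of exclusion b. The conclusion assumes that the parts not available add no ECG step.

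Three stronger readings are not supported: that any site in fact omits the ECG, that a recognised long QTc could not be acted on, and that a given number of patients would be harmed. The number affected cannot be derived from the documents. The sample size of 600, the error rates and the comparison between arms do not depend on this point. The change is nevertheless worth making, because the protocol itself names the hazard and the ECG is already one of its listed options.

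**What to change.** In item 5c, replace the cardiac alternative with: *ECG with QTc recorded before the first dose; cardiac monitoring may be added but does not replace it.* The timing words are essential, because an ECG taken after dosing has begun would not serve the screening aim. Because treating staff are blinded, the requirement has to apply to all patients in both arms.

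Exclusion b needs no rewording for this to work: it is open-ended and covers starting as well as continuing the drug, so the investigator can act on the reading.

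The cost is one wording change, a slightly longer screening step and a few more exclusions. If the procedures manual or another part of the protocol already requires a pre-dose ECG, the edit only aligns 5c with it.

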**6. Specific protocol interventions:**

- a. Subjects entering the experimental group will receive hydroxychloroquine orally or by nasogastric tube (refer to the protocol procedures manual for the method of crushing tablets and administration via nasogastric tube), 200 mg every 12 hours, for 10 days. The placebo group will receive an identical placebo for 10 days. 10 days are tentatively proposed although the working groups suggest a use between 5 to 14 days; the box of hydroxychloroquine contains 20 tablets of 200mg; We justify the 10-day period because it is somewhere in between the various recommendations and because it is more practical to use one box per subject
- b. Patients in both strata will be treated according to protocols of participating institution under the responsibility of the physician in charge: all interventions, medications for all purposes, or non-drug interventions will be registered.
- c. Patients will be followed up to 30 days after randomization by telephone if discharge occur earlier than Day 30
- d. The Investigator is responsible for detecting, documenting, and recording events that meet the definition of an AE or SAE and remain responsible for following up AEs that are serious, considered related to the study

intervention or study procedures, or that caused the participant to discontinue the study

- e. Adverse events will be reported to CE and to manufacturer of the drug (Sanofi México, S.A. de C.V.)

**Statistical analysis:** The analysis will be carried out in R-Rstudio statistical software. Descriptive statistics will be used according to the type of variable and distribution.

The main outcomes will be compared using parametric and non-parametric tests according to the type of variable and distribution.

Death rate (at 30 days), the primary outcome, will be compared between treatment groups using a logistic regression model, adjusting for age, time from onset of symptoms to randomization, comorbidities (diabetes, hypertension, obesity, tobacco smoking) taking into account the randomization strata.

From the secondary endpoints, proportion of patients needing mechanical ventilation, will be compared also by a similar logistic regression model as that proposed for 30 days-death rate. Days of mechanical ventilation, days of hospitalization and days of oxygen therapy will be compared in a multivariate model, including an indicator of randomization strata, adjusting for confounding variables (age, time from onset of symptoms to start of treatment, and comorbidities, especially diabetes, obesity, tobacco smoking, hypertension)

We also will compare time to death and time to a negative viral test, adjusting for confounding variables (age, time from onset of symptoms to start of treatment, comorbidities) using the Cox proportional hazards model.

There will be a CMDS, a multidisciplinary advisory group, made up of an expert in statistics, a clinical researcher, an expert in ethics and a clinician related to influenza and coronavirus, none involved in the clinical trial and therefore independent, who in the middle of the Trials will have access to the data and the randomization code to evaluate the data including safety and efficacy results. The study results will remain blinded to trial team and sponsor representatives, so that not to impact final interpretation of the study results.

**Clinical Researcher:** [name], clinical pharmacologist, anesthesiologist and intensivist who will act as coordinator. Dra. [name], Ear nose and Throat specialist and with a masters degree in medical sciences.

**Statistics:** [name], Head of the Department of Epidemiology of INER.

**Ethics:** [name], medical director of INER

**Clinician:** [name], Infectologist, expert in influenza-like infections and now in COVID-19 infection

The aim of the committee is to assess the advantages and disadvantages of continuing the trial in the analysis in the middle of the sample, especially if it is considered ethical to continue the recruitment, given the results found in the middle of the study.

In principle, there are no controlled studies with which to compare but they may appear in the course of the trial.

An interim analysis is planned, upon completing half of the sample, that can identify if a noticeable difference is found in the main outcome measure, demonstrating an advantage in effectiveness, which, due to its magnitude, leads to stopping the trial.

Also, to indicate significant adverse effects or toxicity.

The final statistical analysis will be carried out taking into account this intermediate analysis. The CMDS will provide a written report (not accessible to anyone outside the CMDS) of its observations. It will be considered sufficient to stop the trial because efficacy in the first interim analysis (1 interim and final), if  $P < 0.0054$  and the final analysis will remain significant with  $p < 0.0492$  (according to O'Brien-Flemming). It can also be stopped if probability of success at the final analysis, given the interim results, is too low.

1. **Sample size:** Mortality reported in severe COVID-19 ranges depending on the source, but in China among hospitalized patients with pneumonia has been reported from 4-15% (1,2,4). The WHO suggests at least 400 subjects for sample estimation in clinical trials evaluating therapies for COVID-19, although severe outcomes or deaths increase considerably in hospitalized patients or those in intensive care as those eligible for this trial. (3). At the moment, many behavioral characteristics and outcomes of COVID-19 are unknown, especially in our setting; For this reason, we used the estimate of a mortality of around 15% in severe COVID-19 with a 50% reduction in mortality with treatment, obtaining in the sample calculation a number of subjects similar to that recommended by the WHO.

- a. 2-tailed significance level 95, alpha 5%
- b. Potency (1-beta, chance of detection): 80%
- c. Treaties vs. controls 1: 1
- d. Estimated mortality in controls 15%
- e. Estimated mortality in experimental 7.5%, reduction in mortality of 7.5%, which is 50% (RR 0.5).

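### The primary mortality model leaves out baseline oxygenation, which entry already requires to be documented; pre-specifying it, properly coded, is a cheap and modest gain in power.

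*Protocol*

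**What the plan says.** The primary outcome is "Mortality rate at 30 days after randomization" (Protocol, Main outcome). Under Statistical analysis in section 3.4 the two arms are to be compared on it by logistic regression. The protocol fixes the covariates of that model in the same sentence: "adjusting for age, time from onset of symptoms to randomization, comorbidities (diabetes, hypertension, obesity, tobacco smoking) taking into account the randomization strata". Besides treatment, that makes six named covariates and the stratum. The secondary models that follow repeat age, symptom duration and comorbidities. None of them lists oxygenation.

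Entry criterion e admits only patients with "Hypoxemic type respiratory failure, documented by a SaO 2 <90% in ambient air, or a PaO 2 / FIO 2 <250". Those cut-offs apply at 2240 m, with "values equivalent to other altitudes above the sea level" elsewhere.

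The strata are defined in section 3.4 under Risk stratification. Stratum B is patients "requiring invasive ventilatory management and / or management in the intensive care respiratory unit at the time of randomization". Stratum A is hospitalized patients who do not need invasive ventilation.

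**The concern.** Hypoxemia defines the disease under study, and a value for it must exist for every patient at entry. The protocol's introduction itself ties respiratory severity to death: 10-15% in severe hospitalized cases, rising to 20-30% with intensive care and ventilation. Yet the fixed list has tobacco smoking and no measure of how hypoxemic the patient was.

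The two-level stratum covers severity only coarsely. Stratum A pools everyone not needing invasive ventilation, and stratum B mixes ventilated patients with others in intensive care. Some secondary analyses lack even that proxy. Need for invasive ventilation is assessed in stratum A only, where the stratum term is constant. The Cox models for time to death and time to a negative viral test name no strata.

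At stake is some power, and protection if the arms happen to differ in oxygenation at baseline.

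**Working it through.** **1. The plan's own figures.** Inputs from the Sample size item: mortality 15% v 7.5%, 1:1 allocation, 80% power, "2-tailed significance level 95, alpha 5"%. With p̄ = 0.1125 and d = 0.075:

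- Fleiss: n = [1.960·√(2 × 0.1125 × 0.8875) + 0.842·√(0.15 × 0.85 + 0.075 × 0.925)]² / 0.075² = 278 (stated 279).
- Fleiss with continuity correction: 304 (stated 305).
- Kelsey: (1.960 + 0.842)² × 2 × 0.1125 × 0.8875 / 0.075² = 278.6, so 279 (stated 280).

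The figures reproduce to within two patients. At 300 per group, unadjusted power is 83.0% at two-sided 0.05 and 82.8% at the final level of 0.0492.

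**2. Deaths per model term.** Expected deaths are 300 × 0.15 + 300 × 0.075 = 67.5. The listed model has 8 terms (treatment, six covariates, stratum): 67.5/8 = 8.4 per term. One more term gives 67.5/9 = 7.5, and two more give 67.5/10 = 6.75.

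**3. Power without and with oxygenation.** Simulation of 600 patients, 3,000 trials per scenario, marginal mortality held at 15% v 7.5%, allocation stratified, Wald test at 0.0492. Assumptions not in the protocol: 30% in stratum B, stratum OR 2.0, age OR 1.8 per SD, small effects for the other covariates, and one clean continuous oxygenation variable.

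| Oxygenation OR per SD | Uncorrelated with stratum | Correlation 0.5 with stratum |
|---|---|---|
| 1.0 | 83.3% v 83.5% | 85.2% v 85.4% |
| 1.3 | 83.7% v 83.9% | 86.5% v 86.9% |
| 1.5 | 85.4% v 86.2% | 86.3% v 86.1% |
| 2.0 | 85.2% v 87.0% | 85.9% v 87.6% |
| 2.5 | 83.8% v 87.5% | 86.3% v 88.4% |

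A second simulation used 4,000 trials per scenario and different assumptions (40% in stratum B, stratum log-OR 0.9, age log-OR 0.5 per SD). It gave 84.6% v 84.9%, 84.4% v 85.8% and 85.2% v 88.7% at within-stratum ORs of 1.5, 2.0 and 2.5, and 84.9% v 85.0% with no effect. Type I error was 5.1% to 5.3%.

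**4. Where the gain comes from.** At OR 2.0 (uncorrelated), the treatment log-OR moves from -0.841 to -0.893 and its standard error rises from 0.287 to 0.297. The gain in effective sample size is (0.893/0.297)² / (0.841/0.287)² = 1.05. At OR 2.5 it is (0.925/0.304)² / (0.835/0.287)² = 1.09. Across scenarios it is worth about 0% to 10% more patients.

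**5. Chance imbalance.** The SD of the standardized difference between arms is √(2/300) = 0.082, so the 95% limit is 1.96 × 0.082 = 0.16 SD. Left unadjusted, a difference of that size multiplies the treatment OR by exp(0.16 × ln OR): 1.04, 1.07, 1.12 and 1.16 at ORs of 1.3, 1.5, 2.0 and 2.5 per SD. At OR 2.0 that is ln(1.12)/0.287 = 0.4 standard errors. At this limit a result at z = 2.0 (p about 0.046) would become z = 1.6 (p about 0.11).

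**6. Can the two entry measures share a column?** Not on the raw scale. On room air (FIO2 0.21), a saturation of 85% gives 85/0.21 = 405, and any saturation above 250 × 0.21 = 52.5% gives a ratio above 250. Patients qualifying by PaO2/FIO2 at 2240 m lie below 250. A column holding both ratios would mainly record which measure was taken. In simulation such a column lost most or all of the gain. Values kept on each measure's own scale, with an indicator for the measure, recovered most of it.

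**The case against.** The strongest reply is that nothing here is wrong. The model is pre-specified, the test is valid under randomization, the strata bring ventilation and intensive care into it, and power exceeds the planned 80% without the extra term. Entry cut-offs also truncate the range of oxygenation, which limits what it can add. The protocol gives no prognostic strength for it, and only the stronger assumed effects yield more than about 1.5 points. The simulations in steps 3 and 4 used one clean variable; measurement error, missing values or mixed scales would generally shrink the gain. All of that stands, and it is why the point is minor.

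A reader might go further and infer that the plan sacrifices precision, or that the covariate is free. Neither follows. On the log-OR scale the standard error rises slightly, and the gain is in power because the conditional estimate moves away from zero. Nor is it free: criterion e accepts either of two measures and gives no altitude conversion, so a common coding has to be defined and recorded. A reader might also infer bias. Chance imbalance is already reflected in the test's error rate and is not bias.

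What the reply does not remove is that the list is fixed in the protocol, that a value of the omitted variable must exist for every patient, and that including it costs no power even when it is not prognostic.

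**Conclusion.** The point holds as a worthwhile improvement of low severity. The planned primary analysis is legitimate and adequately powered on its own inputs. Adding baseline oxygenation would give about 0 to 4 points of power and protect against a chance difference in severity that, at its 95% limit, could shift the treatment OR by a factor of 1.04 to 1.16. Both ranges rest on assumed effects of OR 1.3 to 2.5 per SD, and the power figures also on the assumed stratum mix and covariate effects. The benefit in the secondary models was not simulated. The documents do not support reading the omission as an invalid test, an underpowered trial, or a reason to drop a listed covariate.

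**What to change.** Under Statistical analysis in section 3.4, add baseline oxygenation to the covariates of the primary logistic model and of the matching secondary models. Fix the coding in advance in one of two ways:

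- one common measure, defined and recorded for all patients; or
- the qualifying value, in altitude-equivalent terms by a stated conversion, standardized within its own measure, plus an indicator of whether SaO2 or PaO2/FIO2 was used. State which value counts when a patient has both.

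Do not enter PaO2/FIO2 and an unconverted saturation/FIO2 ratio in one column. Keep every listed covariate, including smoking.

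The cost is one or two more model terms (7.5 or 6.75 expected deaths per term instead of 8.4), and recording the qualifying value and FIO2 on the case report form. No new procedure is needed if the qualifying value is used. The common-measure option would need that measure taken in patients who qualified by the other.
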